# Study protocol for a randomised pragmatic trial comparing the clinical and cost effectiveness of lithium and quetiapine augmentation in treatment resistant depression (the LQD study)

**DOI:** 10.1186/s12888-017-1393-0

**Published:** 2017-06-26

**Keywords:** Treatment resistant depression, Lithium, Quetiapine, Pragmatic, Randomised clinical trial, Longitudinal, Open-label, Multi-centre, Augmentation, Superiority design

## Abstract

**Background:**

Approximately 30–50% of patients with major depressive disorder can be classed as treatment resistant, widely defined as a failure to respond to two or more adequate trials of antidepressants in the current episode. Treatment resistant depression is associated with a poorer prognosis and higher mortality rates. One treatment option is to augment an existing antidepressant with a second agent. Lithium and the atypical antipsychotic quetiapine are two such add-on therapies and are currently recommended as first line options for treatment resistant depression. However, whilst neither treatment has been established as superior to the other in short-term studies, they have yet to be compared head-to-head in longer term studies, or with a superiority design in this patient group.

**Methods:**

The **L**ithium versus **Q**uetiapine in **D**epression (**LQD**) study is a parallel group, multi-centre, pragmatic, open-label, patient randomised clinical trial designed to address this gap in knowledge. The study will compare the clinical and cost effectiveness of the decision to prescribe lithium or quetiapine add-on therapy to antidepressant medication for patients with treatment resistant depression. Patients will be randomised 1:1 and followed up over 12 months, with the hypothesis being that quetiapine will be superior to lithium. The primary outcomes will be: (1) time to all-cause treatment discontinuation over one year, and (2) self-rated depression symptoms rated weekly for one year via the Quick Inventory of Depressive Symptomatology. Other outcomes will include between group differences in response and remission rates, quality of life, social functioning, cost-effectiveness and the frequency of serious adverse events and side effects.

**Discussion:**

The trial aims to help shape the treatment pathway for patients with treatment resistant depression, by determining whether the decision to prescribe quetiapine is superior to lithium. Strengths of the study include its pragmatic superiority design, broad inclusion criteria (external validity) and longer follow up than previous studies.

**Trial registration:**

ISRCTN registry: ISRCTN16387615, registered 28 February 2016. ClinicalTrials.gov: NCT03004521, registered 17 November 2016.

## Background

Major depressive disorder (MDD) is a highly prevalent and disabling illness requiring effective treatment in order to reduce symptom severity and improve quality of life [1, 2]. Current clinical guidelines recommend the use of antidepressant medication in cases of moderate to severe MDD [3]. However, approximately 30–50% of patients fail to adequately respond to both first and second line antidepressant treatment trials, and can therefore be described as treatment resistant [3–5]. Existing evidence clearly indicates that the prognoses for patients with treatment resistant MDD (TRD) can be improved with adequate multimodal and/or successive treatment trials [4, 6]. Given that TRD is associated with a generally poorer prognosis, higher mortality rates and higher healthcare utilisation costs than MDD alone [7, 8], the importance of ensuring that the most effective available medication is fully utilised in clinical practice is clear.

Treatment options for patients with TRD include increasing the dose of a patient’s existing antidepressant, switching to another antidepressant (same or different class), or augmenting the existing antidepressant medication with a second agent, for example an additional antidepressant, mood stabiliser, or antipsychotic medication [3]. Increases in dosage have been associated with increased efficacy for some antidepressants [7, 9–11] but not for others [12–15]. Switching to an alternative antidepressant is generally suggested in cases where a patient has either made no response, or is not tolerating their current medication [3], but remission rates to third or fourth line antidepressant treatments are in the order of just 10–15% [4]. For TRD patients in whom there has been a partial response to current antidepressant treatment, augmentation is usually recommended [3]. However, beyond these general principles, there remains much uncertainty about when to switch and when to augment treatments.

One augmentation strategy is to prescribe a combination of antidepressant medications. However, recent evidence from a large randomised controlled trial indicated that this approach is no more effective than antidepressant monotherapy, questioning its appropriateness [16]. The use of lithium or atypical second-generation antipsychotic augmentation is an approach supported by several recent meta-analyses [17, 18]. This is reflected in the National Institute of Clinical Excellence (NICE) and the British Association for Psychopharmacology (BAP) treatment guidelines, which emphasise that add-on treatments are a standard treatment pathway for TRD, and include lithium and newer atypical antipsychotics, such as quetiapine, aripiprazole, olanzapine and risperidone, as first line options [3, 19].

Despite these recommendations, few studies have compared the efficacy of lithium versus atypical antipsychotic augmentation head-to-head [3, 20, 21]. The largest and arguably best study to date compared lithium and quetiapine extended release (XR) over just 6 weeks, and found quetiapine to be non-inferior to lithium add-on therapy in patients with TRD [20]. Lithium versus quetiapine augmentation has also been compared in a pilot study of 20 patients, which reported significant reduction in depressive symptoms in both groups, but a greater decrease in Hamilton Depression Rating Scale (HDRS) scores from day 14 onwards in the quetiapine group [21]. However, neither of these comparisons have included a long term follow up, which is needed to ensure that the most effective treatment option is fully utilised in clinical practice, particularly given the chronic nature of TRD, the associated high rates of relapse [8], and the fluctuating nature of depressive symptoms (even in those responding to acute phase treatment) [16]. Clinical guidelines also advise that responders should continue taking the effective medication for at least 6–12 months [3, 19]. Therefore a clinical trial comparing lithium and quetiapine augmentation, with frequent assessment of symptoms and 12 month follow up is clearly warranted.

In the present study, lithium augmentation will comprise one treatment arm, as it is the first-choice add-on treatment for patients with TRD according to the World Federation of Societies of Biological Psychiatry Task Force [22], and a first line treatment option recommended by NICE and BAP [3, 19]. Quetiapine was selected as the atypical antipsychotic comparator, as there is strong evidence for the efficacy of quetiapine augmentation versus placebo [23–25], and it is currently licenced for marketing as an add-on treatment for TRD in the UK in its XR formulation [19]. Although NICE does support the use of other atypical antipsychotics (aripiprazole, risperidone and olanzapine) as add-on treatments in TRD, and there is some evidential support for their use [17, 26], quetiapine is the only atypical antipsychotic to have been previously studied under trial conditions in a head-to-head comparison with lithium, meaning at least comparable short-term effectiveness between the two treatments under trial conditions is known [20]. While this study by Bauer and colleagues reported quetiapine to be non-inferior to lithium over a six week treatment course, there was also some indication that quetiapine may be more clinically effective than lithium. This included lower depression severity scores (Montgomery-Åsberg Depression Rating Scale, MÅDRS), reported as early as day 4 of treatment, and less sleep disturbance [20]. Additionally, a network meta-analysis comparing augmentation agents in TRD found lithium and quetiapine to both be more effective than a placebo, but indicated that the efficacy of quetiapine was more robust than lithium [27].

### Objectives and hypothesis

This study aims to determine whether the decision to prescribe quetiapine is more clinically and cost effective than the decision to prescribe lithium over a longer term in a randomised clinical trial powered to detect superiority. We propose a 12 month follow up period, hypothesising that quetiapine will be superior to lithium in terms of our primary outcomes: time to all-cause treatment discontinuation and average depressive symptom burden over 12 months.

We hope to help shape a modified treatment pathway for TRD in which one augmenter is preferential to the other. However, if quetiapine is not found to be clinically superior based on our primary and secondary outcomes, the results of the cost effectiveness analysis, or individual level predictive factors, may determine the most appropriate choice for each patient.

The trial will recruit patients with TRD: defined as the failure to adequately respond to two or more therapeutic trials of antidepressant treatments in the current episode (at adequate dose and duration) [3, 8]. This definition of treatment resistance is in line with the point at which treatment augmentation is recommended in clinical practice [3] and at which the evidence suggests clinical equipoise between the two treatments [20].

This protocol paper is consistent with SPIRIT (Standard Protocol Items: Recommendations for Interventional Trials) 2013 recommendations [28] (checklist attached).

## Methods/design

### Study design

LQD is a phase 4, 12-month, parallel group, multi-centre, patient 1:1 randomised, pragmatic, open-label, superiority trial, comparing the clinical and cost-effectiveness of the decision to prescribe lithium versus quetiapine as add-on treatment to antidepressant medication in patients with TRD.

### Participants

We will recruit participants who fulfil the following inclusion criteria:Under the care of a GP and/or adult mental health servicesCurrent episode of depression meeting Diagnostic and Statistical Manual of Mental Health Disorders – Fifth Edition (DSM-5) [29] criteria for MDD (single or recurrent episode) assessed using the Mini International Neuropsychiatric Interview, Version 7 (MINI 7.0) [30]HDRS - 17 item [31] score ≥ 14 at screeningAny gender and aged 18 years or overTRD [3, 32]: defined as failing to adequately respond to at least two antidepressant therapies, prescribed for at least 6 weeks at minimum therapeutic dose, as determined by the Maudsley Prescribing Guidelines (MPG) and/or British National Formulary (BNF) [33, 34]Current antidepressant treatment has remained unchanged for ≥6 weeksProvision of written, informed consent

Exclusion criteria for participants are:Diagnosis of bipolar disorder (defined as meeting DSM-5 criteria for bipolar 1 or 2) on the MINI 7.0Diagnosis of current psychosisUse of lithium or quetiapine during current depressive episodeOngoing use of another atypical antipsychoticKnown contraindication to use of either lithium or quetiapineCurrently participating in another clinical trial of an investigational medical productInsufficient degree of comprehension or attention to be able to engage in trial proceduresPregnancy, actively trying for pregnancy, or breastfeeding

### Recruitment procedure and assessments

Participant recruitment will take place across three of the UK National Institute of Health Research (NIHR) Clinical Research Network hubs: South London, the North East and North Cumbria, and Thames Valley and South Midlands. Recruitment is underway at four sites within these hubs: the South London and Maudsley National Health Service (NHS) Foundation Trust (SLaM); Northumberland, Tyne and Wear NHS Foundation Trust (NTW); Oxford Health NHS Foundation Trust (OHT); and Tees, Esk and Wear Valleys NHS Foundation Trust (TEWV).

Potential participants will be identified primarily at routine secondary care clinic appointments or via Consent for Contact initiatives within the trusts (e.g. http://www.slam.nhs.uk/research/patient-involvement/current-opportunities/consent-for-contact) alongside advertisements, and via Participant Identification Centres including primary care and external UK NHS trusts to enhance recruitment.

### Randomisation and blinding

The study will randomise individual participants 1:1 to the decision to prescribe lithium or quetiapine, stratified by recruiting region (London, Oxfordshire, or North East England), depression severity (HDRS-17), and TRD severity (failure of two / three or more antidepressant treatments in the current episode), using block randomisation with randomly varying block size. Randomisation will be conducted by a trial researcher using an independent online service provided by UK Clinical Research Collaboration registered King’s Clinical Trial Unit, with unique patient identification numbers generated by the InferMed MACRO system.

This is an unblinded study, whereby treating clinicians, trial researchers, and patients will be aware of the treatment allocation for patients where applicable to their role. In order to reduce the potential for assessor bias, the following clinician-rated assessments will be completed at follow up visits by an assessor who is blind to the patient’s medication (face-to-face or via phone): 1) MÅDRS [35], and 2) Clinical Global Impressions scale (CGI) [36]. Trained trial researchers and clinicians may perform blinded assessments, but must not have access to the trial database for the relevant site to reduce the likelihood of unblinding (access to the trial database is granted on a site by site basis, dependent on role). The blinded assessor will remind the participant not to reveal treatment allocation at the start of the assessment and will confirm they remained blinded to treatment allocation throughout the assessment.

### Primary outcomes

Difference in time to all-cause treatment discontinuation over 12 months post-randomisation between lithium and quetiapine using survival analysis methods, with time being between the first prescription and discontinuation of the medication to which the patient was randomised.Longitudinal Depression Severity: the difference in the area under the curve between lithium and quetiapine over 12 months post-randomisation in the self-rated Quick-Inventory of Depressive Symptomatology (QIDS-SR) [37], assessed weekly via the True Colours system (www.truecolours.nhs.uk), using a linear mixed model, covarying for baseline QIDS-SR score.

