### Secondary outcomes

The secondary outcomes will be measured at 8 and 52 weeks, and differences between lithium and quetiapine assessed at both time points. Continuous secondary outcomes measured over time will use appropriate generalised linear models, covarying by baseline score where applicable. Where there are repeated measures of a continuous variable, the analysis will be set in the mixed model framework. Time to event variables will be analysed using survival methods. The secondary outcomes are as follows:Clinician-rated depression severity (continuous total score on the MÅDRS).Clinician-rated response and remission rates (defined as proportion with ≥50% reduction in baseline MÅDRS total score and MÅDRS total score ≤ 10, respectively).Global improvement (proportion of patients with a CGI-improvement score of ‘much’ or ‘very much improved’).Health-related quality of life (summary index EuroQol-5D, EQ-5D score [38]).Social functioning (continuous total Work & Social Adjustment Scale (WSAS) score [39]).Self-report adherence to treatment (5-item Medication Adherence Report (MARS-5) continuous total scores and exploratory cut-offs categorising patients as either adherent or non-adherent [40]).Physical health parameters: weight (kg) and blood pressure (mmHg).Time to commencement of trial medication from randomisation (and number of patients commencing therapy in each arm).Time to uptake of a new intervention for depression from randomisation (pharmacological or non-pharmacological) over 12 months (and proportion of patients in each arm receiving new interventions).Side Effects (continuous total score on the Patient Rated Inventory of Side Effects (PRISE) [41]).Frequency of Serious Adverse Events (SAEs).

Secondary outcomes, except for SAEs, will be adjusted for multiple comparisons. SAEs will be tabulated as number of SAEs in each group, and number of people reporting an SAE in each group over 12 months. We will also summarise the reasons for clinicians not prescribing and patients not commencing the medication they are randomised to, reasons for treatment discontinuation, the number of withdrawals, and the reasons for withdrawals from the trial. However, we will not test the difference between the groups on these variables statistically.

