In this trial, patients will be randomised to *the decision* to prescribe either lithium or quetiapine. This means that in each case, the treating trial clinician will decide whether or not to prescribe the medication that the patient has been randomised to, according to their clinical judgement. It is therefore possible that a small proportion of randomised patients will not receive the medication that they are allocated to. This may be due to a previously unknown contraindication to the study medication arising during the pre-prescribing safety checks (exclusion criteria for trial entry is *known* contraindications to lithium or quetiapine only). The required safety checks are: electrocardiogram, if clinically indicated (both treatment arms) and pre-lithium blood tests (renal function, thyroid function, full blood count, serum calcium). These tests must be conducted prior to prescription, unless they have been completed within a sufficiently recent period according to the prescribing clinician’s judgement.

All patients will be followed up for 12 months, regardless of medication status. It is expected that a significant proportion of patients will fail to respond or tolerate the medication and will terminate treatment before 12 months. Treatment may also be extended beyond the follow up period at the discretion of the patient’s clinician. All concomitant pharmacological and non-pharmacological interventions are permitted throughout the duration of the trial and will be recorded by the trial team.

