### Statistical methods for analysing primary and secondary outcomes

A full statistical analysis plan will be drawn up prior to completion of data collection. The main analysis will follow an intention to treat (ITT) principle, whereby patient data are analysed by treatment group, regardless of the medication status of patients throughout the follow-up period.

Participant flow will be presented in a CONSORT diagram. For analysis of the listed primary and secondary outcomes, missing baseline data will be filled in using imputation [47]. Models will covary for randomisation stratification factors throughout. For the self-report QIDS-SR score a linear mixed model, covarying by baseline score, will be used for the estimation of the mean treatment difference and 95% confidence interval (CI) over the course of the trial. Full information maximum likelihood methods will be used for analysis, which will account for missing data under the missing at random assumption. Error distributions will be checked using Q-Q plots. Time to discontinuation will be calculated from first prescription date to treatment discontinuation, and will be analysed using Kaplan-Meier methods and Cox regression models, providing the hazard ratio for treatment discontinuation in lithium versus quetiapine, and associated 95% CI.

Continuous secondary outcomes measured over time will use generalised linear models appropriate to the variable distribution covarying by baseline where applicable, and using mixed models where there are repeated measurements. Adjustment for multiple testing will be presented [48].

For measures where missingness is above 5% and where the absence of repeated measurement gives less confidence in the adequacy of the missing data properties of maximum likelihood, we may undertake a sensitivity analysis within a multiple imputation framework [49].

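### The discontinuation primary outcome is timed from first prescription, so randomised patients who are never prescribed the allocated drug have no time origin in an analysis described as ITT

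*Protocol article*

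**What the plan says.** Two sections of the protocol article set the same time origin. Primary outcomes defines discontinuation "with time being between the first prescription and discontinuation of the medication to which the patient was randomised". Statistical methods for analysing primary and secondary outcomes says: "Time to discontinuation will be calculated from first prescription date to treatment discontinuation".

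Other statements point to randomisation as the origin:

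- Randomisation and blinding: "The study will randomise individual participants 1:1 to the decision to prescribe lithium or quetiapine".
- Primary outcomes opens the same definition with "Difference in time to all-cause treatment discontinuation over 12 months post-randomisation between lithium and quetiapine using survival analysis methods".
- The statistical methods section sets an ITT main analysis in which "patient data are analysed by treatment group, regardless of the medication status of patients throughout the follow-up period".

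Interventions acknowledges non-prescription: "It is therefore possible that a small proportion of randomised patients will not receive the medication that they are allocated to". One reason it gives is a contraindication that comes to light during pre-prescribing checks, which it lists as "electrocardiogram, if clinically indicated (both treatment arms) and pre-lithium blood tests (renal function, thyroid function, full blood count, serum calcium".

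Secondary outcomes has a separate measure, "Time to commencement of trial medication from randomisation", with the number commencing in each arm. Reasons for not prescribing and not commencing are summarised without a test. Nothing in the article gives a never-prescribed patient an event or censoring time in the primary outcome.

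**The concern.** The question posed is what happens when a clinician decides to prescribe one drug rather than the other. Not being able to go through with that decision is part of the answer. A clock that starts at first prescription compares only the patients who got past that step, and the step comes after randomisation, in an open-label trial, with blood tests required for one drug only. If non-prescription differs by arm, or removes a particular kind of patient, the compared groups are no longer the randomised ones. A real difference between the two decisions could be hidden, or an apparent difference could arise from selection. The outcome is one of the two primary outcomes and it determined the lower limit of the sample size.

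**Working it through.** **1. The plan's own figure.** Power calculation assumes 50% (lithium) and 70% (quetiapine) still on treatment at 52 weeks, two-sided alpha 0.05, 276 randomised, 10% loss, hence 248.4 patients.

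- HR (quetiapine vs lithium) = ln(0.70)/ln(0.50) = 0.515.
- Expected events = 248.4 × (0.50 + 0.30)/2 = 99.4.
- Schoenfeld: Φ(√99.4/2 × |ln 0.515| − 1.96) = 91.2%.
- Freedman: Φ(√99.4 × (1 − 0.515)/(1 + 0.515) − 1.96) = 89.2%.
- Two proportions: 124 per arm, 248 in all; 248/0.9 = 275.6, rounded up to 276.

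The stated 90% reproduces. The only deduction is the 10% loss; there is none for patients never prescribed.

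**2. Who has a time zero under the stated rule.**

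| Patient | First prescription date | Place in the analysis as written |
|---|---|---|
| Prescribed and started | Yes | Included |
| Prescribed, never started | Yes | Included, but discontinuation date undefined |
| Never prescribed | No | No time origin |

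Only the last group is lost.

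**3. What the loss could hide.** The document gives no never-prescribed rate, so the shares p are assumptions. Take 52-week retention of 60% among prescribed patients in both arms; the planned analysis then shows HR 1.00. Counting never-prescribed patients as not retained, S = 0.6 × (1 − p) and HR = ln(S_Q)/ln(S_L).

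| Never prescribed, lithium/quetiapine (assumed) | S_L | S_Q | All-randomised HR |
|---|---|---|---|
| 5%/5% | 0.570 | 0.570 | 1.00 |
| 5%/2% | 0.570 | 0.588 | 0.94 |
| 10%/5% | 0.540 | 0.570 | 0.91 |
| 20%/5% | 0.480 | 0.570 | 0.77 |

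These HRs are ratios of log 52-week retention. Day-0 events are not proportional hazards, so they are approximate.

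**4. What selection could create.** Assume no drug effect, 30% of patients with 30% retention and the rest with 70%, and all never-prescribed patients drawn from the first group. At 20%/5%:

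- lithium: (0.10 × 0.3 + 0.70 × 0.7)/0.80 = 65.0%;
- quetiapine: (0.25 × 0.3 + 0.70 × 0.7)/0.95 = 59.5%;
- HR = ln(0.595)/ln(0.650) = about 1.21 for identical drugs.

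At 10%/5% it is about 1.06. This runs the opposite way to step 3.

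**5. Power under each clock.** This takes 50%/70% as retention among prescribed patients, with 124.2 per arm before non-prescription (Schoenfeld).

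| Never prescribed (assumed) | Prescription clock, prescribed only | Randomisation clock, all patients |
|---|---|---|
| 5%/5% | 89.8% (236 patients) | 87.5% (47.5% vs 66.5%) |
| 10%/5% | 88.7% (230) | 94.1% (45.0% vs 66.5%) |
| 20%/5% | 86.3% (217) | 99.2% (40.0% vs 66.5%) |
| 20%/20% | 84.2% (199) | 73.9% (40.0% vs 56.0%) |

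If 50% and 70% were meant as proportions of all randomised patients, the stated power already applies to the randomisation clock.

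**The case against.** The article nowhere says that never-prescribed patients are excluded. It promises ITT and a full analysis plan, which might code them in some way. That is fair as far as it goes: exclusion is the consequence of the rule, not a stated intention. But the origin is written twice in matching terms, so a later plan would have to override it rather than fill a gap.

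Persistence after prescription is a legitimate measure. The Discussion describes the primary outcomes as effectiveness and tolerability, and initiation has its own secondary outcome timed from randomisation. This also stands, and is a reason to keep the prescription-origin analysis. It does not make that analysis an ITT comparison of the two decisions.

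The illustrations use invented shares. The protocol says only that the proportion is small, excludes known contraindications at entry, and lets clinicians rely on sufficiently recent test results. A 20% lithium share is hard to call small, and the 5%/2% case gives only 0.94. This limits what can be claimed about size.

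A reader might go further in four ways that the document does not support:

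- *Patients who are prescribed the drug but decline to take it are also lost.* They have a first prescription date. Their problem is the missing definition of when they discontinued.
- *Later starts bias the comparison through shorter observation windows.* Earlier administrative censoring is handled by Kaplan-Meier and Cox methods when it is non-informative.
- *The sample size is wrong.* The 90% reproduces.
- *ITT fails for the trial as a whole.* The QIDS-SR outcome is followed for 12 months from randomisation whatever the medication status.

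**Conclusion.** The point holds for the first primary outcome and for never-prescribed patients. The stated origin conflicts with the unit of randomisation, the 12-month window in the same definition, and the ITT statement; followed as written, it removes randomised patients through a step taken after allocation. That the removal differs by arm is a plausible inference from the lithium-only blood tests and open-label prescribing, not an established fact. Size and direction cannot be derived from the document: under assumed shares the planned HR of 1.00 corresponds to about 0.94 to 0.77 in all randomised patients, while selection alone could produce about 1.06 to 1.21 in the other direction. If non-prescription proves rare and balanced, the numerical effect will be small, but the analysis would still answer a narrower question than the one posed.

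**What to change.** In Primary outcomes and in the statistical methods section, define the outcome as time from randomisation to being off the allocated drug, in all randomised patients, censored at 52 weeks after randomisation or at last known status. Count patients who are never prescribed or never start as not on allocated treatment from day 0, with a small positive time so that they enter the Cox model. This does not need the date of a decision not to prescribe, which the article does not say is recorded. Add a rule for patients lost before any start is known. Keep the first-prescription analysis as a labelled supportive analysis of persistence.

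The cost is wording. Randomisation dates, start dates and reasons for not starting are already collected. The downsides should be stated:

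- The outcome combines non-initiation with discontinuation.
- Power may fall somewhat if non-prescription is similar in both arms (about 87.5% against 89.8% at an assumed 5%/5%).
- Early events may break proportional hazards, so the Kaplan-Meier difference in 52-week retention should be reported beside the HR.

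As the trial is open-label, the change should be made before outcome data by arm are examined.
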